### The Number of Participants

The primary study end point, DFS is defined as the time following successful surgery to the first date of local, regional/distant relapse or death due to colorectal cancer (patients with secondary malignancy will be censored). Overall survival is defined as the time following successful surgery to death.

In the TaTME, it is assumed that the DFS is 92% and in the RLAR arm 95% at 3 years. A non-inferiority margin of 90% is selected. Based on this estimation, sample size calculation has been done with a one-sided level of significance of 20% and a power of 80%. A total number of 330 patients is needed, 165 patients in the RLAR arm and 165 patients in the TaTME are required with a 10% loss to follow-up assumed.

DFS will be analysed on an intent-to-treat (per protocol) basis using a log-rank test after propensity matching analysis has been conducted; a secondary analysis of DFS will also performed be using a Cox proportional hazards regression model with the unmatched cohort (without adjustment of baseline characteristics, i.e. propensity score match) that allowed for the effect of treatment and include lists of covariate with a statistical interaction of alpha level of 20%.

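### The secondary Cox model for DFS is worded so that it can be read as unadjusted or as covariate-adjusted with a 20% interaction level; about 20 expected events call for a small, prespecified adjusted model

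*Protocol article*

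**What the plan says.** All of the relevant analysis text is in the Protocol article, The Number of Participants. The primary DFS analysis is a log-rank test after propensity matching. Then "a secondary analysis of DFS will also performed be using a Cox proportional hazards regression model", which is to be fitted "with the unmatched cohort (without adjustment of baseline characteristics, i.e. propensity score match) that allowed for the effect of treatment". The same sentence adds that the model will "include lists of covariate with a statistical interaction of alpha level of 20"%. It names no covariates, gives no number of them, and does not say what the 20% level decides.

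Two other statements matter. The Design section says the study is observational and that each patient's technique depends on the centre, each centre performing one technique or the other. The sample-size paragraph gives the rates, "In the TaTME, it is assumed that the DFS is 92% and in the RLAR arm 95% at 3 years", and sets the size at 165 per arm, 330 in all; it adds an assumption, "with a 10% loss to follow-up assumed". No expected number of events is stated.

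**The concern.** The sentence disclaims baseline adjustment, explains that disclaimer as the absence of propensity matching, and then adds covariates. Two analysts could fit materially different models from it and both claim to have followed the plan.

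Each reading has a cost:

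- **Unadjusted.** With allocation by centre, a crude hazard ratio mixes the effect of technique with differences in case mix between centres. It could neither support nor challenge the matched primary analysis.
- **Covariate-adjusted, with interactions at 20%.** Once a treatment-by-covariate term is in the model, the treatment coefficient is the effect at that covariate's reference level, not an overall effect. If the data decide which interaction enters, they also decide what the reported hazard ratio means. A list of covariates plus interactions may also be more than the events can carry.

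This is the only DFS analysis that the section describes for the unmatched cohort. Since matching can discard patients, readers are likely to treat it as the check on the primary result.

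**Working it through.** **Inputs** (Protocol article, The Number of Participants): 3-year DFS 92% (TaTME) and 95% (RLAR); 165 per arm; 10% loss; 20% level attached to interaction.

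**The plan's own figure.** The only stated total is 330 patients. The literal inputs, "with a one-sided level of significance of 20% and a power of 80"%, with 92% against 95%, give by comparison of two proportions

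n per arm = (0.8416 + 0.8416)² × (0.92×0.08 + 0.95×0.05) / 0.03² = 2.833 × 0.1211 / 0.0009 ≈ 381.2, so 382; and 382/0.9 gives 425 after loss.

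This is not 165. The stated margin, "A non-inferiority margin of 90% is selected", has no scale and cannot be entered without a guess. That is a separate matter. The steps below take 165 per arm as given.

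**Expected DFS events at 3 years**

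- TaTME: 165 × (1 − 0.92) = 13.2
- RLAR: 165 × (1 − 0.95) = 8.25
- Total without loss: 21.45
- Total if 10% loss removes 10% of events: 21.45 × 0.9 = 19.3

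**Parameters the events can support, treatment included**

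| Events per parameter | 19.3 events | 21.45 events |
|---|---|---|
| 10 | 1.9 | 2.1 |
| 5 | 3.9 | 4.3 |

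**Sensitivity to longer follow-up.** Table 1 schedules visits to 5 years. If all 5 years entered the model at constant hazard (an assumption), events would be 165 × (1 − 0.92^(5/3)) + 165 × (1 − 0.95^(5/3)) = 21.4 + 13.5 = 34.9, or 31.4 after 10% loss. That is about three parameters at 10 events each, so the conclusion does not change.

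**Chance findings at 20%.** For k independent null interaction tests, P(at least one flagged) = 1 − 0.8^k. The value of k is an assumption, because the article gives none.

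- k = 3: 1 − 0.512 = 49%
- k = 5: 1 − 0.328 = 67%
- k = 8: 1 − 0.168 = 83%

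**Effect on the treatment estimate.** A simulation under no treatment effect (400 runs per setting, about 20 events, eight binary covariates assumed) gave these standard deviations of the treatment log hazard ratio:

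- treatment only: 0.46
- treatment plus eight covariates: 0.51
- interactions also screened at 20%: 0.58

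The variance ratio of the last to the first is (0.58/0.46)² = 1.59, as if 20 events had become 20/1.59 ≈ 13. Rejection at the 5% level was about 3% to 6%, so the harm seen was instability and not clear inflation of type I error. Some fits gave convergence warnings, and the result depends on the eight assumed covariates.

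**The case against.** The strongest reply is that the parenthesis defines its own terms. It glosses the missing adjustment as the propensity match and attaches it to the unmatched cohort. The natural reading is then an ordinary one: the primary analysis uses matched patients, and the secondary uses unmatched patients in a Cox model with treatment and covariates. This stands. A reader might infer that the sentence flatly contradicts itself; the gloss means that only ambiguity is shown.

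Other stronger readings also fail:

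- **That covariates are kept or dropped by a 20% rule.** No retention rule is stated, and grammatically the 20% belongs to the interaction, not to covariate main effects. It could be a liberal level for testing interactions.
- **That the model must be either confounded or overfitted.** Treatment plus one or two prespecified covariates would be neither by construction. The covariate list may properly sit in an analysis plan that is not shown.
- **That the confidence interval will be too narrow.** The simulation does not show this.
- **That this is the only analysis using all 330 patients.** The article does not say which cohort serves overall survival or the other secondary outcomes.

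It is also fair to say that this is a secondary analysis and that the numbers of tests used above are not the plan's.

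The reply does not remove the point. The article does more than leave detail to a later document: it words the adjustment status unclearly and attaches a 20% interaction level to the model that yields the treatment effect, without saying what follows when an interaction meets that level.

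**Conclusion.** The point holds as a matter of ambiguous wording with a real consequence. Taken literally as unadjusted, the model gives a confounded hazard ratio, since technique follows centre. Taken as covariate-adjusted, it has about 19 to 21 DFS events at 3 years, enough for about two parameters at 10 events each or four at 5 each. A covariate list with interaction terms admitted at 20% would exceed that and would make the treatment hazard ratio unstable and conditional on the interaction that entered.

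The event count rests only on the plan's own rates and numbers. The 67% figure assumes five independent null interaction tests, and the loss of precision assumes eight covariates; both illustrate and neither describes the plan. The matched primary analysis is unaffected. The sentence should be rewritten before the analysis.

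**What to change.** Replace the sentence with text that fixes four things:

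1. **Cohort and model.** A Cox model for DFS in the full unmatched cohort, stated plainly to be adjusted.
2. **Adjustment set.** Prespecified and sized to about 20 events: for example, treatment plus the propensity score already estimated for the matching, or treatment plus one to three named prognostic covariates of one parameter each.
3. **Selection and interactions.** No p-value-based selection, and no interaction terms in the model that gives the treatment effect. If interaction tests at 20% are wanted, report them separately as exploratory.
4. **Crude hazard ratio.** Reported as descriptive only.

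The cost is wording; no new data are needed, and the propensity score is already required for the primary analysis. There are trade-offs. The propensity-score version relies on the same score model as the primary analysis, so it is a weaker independent check than direct adjustment for named covariates. Either version deals only with measured case mix. Because each centre performs one technique, neither can fully separate technique from centre. Centre-clustered variance should be used only if there are enough centres; the article does not state how many there are.

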### Data Management

Case report forms (CRFs) will be entered in a secured online page. Only authorized staff at sites will have access via an individual secure login username and password to enter the data. All paper CRFs must be completed, signed/dated and returned to the investigator. Data reported on each CRF should be consistent with the source data or discrepancies should be explained. If information is not known, this must be clearly indicated on the CRF. All missing or ambiguous data will be queried. All sections are to be completed.

All trial records will be archived and securely retained for at least 25 years.

### Ethics and dissemination

The trial will be performed in accordance with the recommendations guiding physicians in biomedical research involving human subjects, adopted by the 18^th^ World Medical Association General Assembly, Helsinki, Finland and stated in the respective participating countries laws governing human research, and Good clinical Practice. The medical ethical committees of all participating countries will have to approve the study protocol prior to enrolling patients. The protocol has been approved by the Danish ethical committee of the Region of Southern Denmark with reference number S-20210038.

## Discussion

To date studies on TaTME and robotic TME have focused mainly on short term outcomes and oncological endpoints such as specimen quality, circumferential resection margin involvement and the free distal margin [13,16,17].

In a recent study comparing TaTME and Robotic TME, there were no differences in the incidence of poor quality. However the authors noted that distal resection margin (DRM) involvement was higher in the TaTME group [16]. They attributed this to the learning curve effect of TaTME. As discussed earlier, previous reports have noted that the learning curve for robotic TME was less than laparoscopic surgery, which in effect TaTME is still a laparoscopic “bottom up” approach.

Nonetheless, the long-term oncological parameters for both procedures, including overall survival, disease-free survival and local recurrence, are yet to be clarified. Secondly, there have been significant concerns in regards to an increased recurrence rate after TaTME [18]. The Norwegian group have noted an unexpected increase in local recurrence after TaTME of 9.5% after a median of 11 months after surgery [18]. The reasons for their observations is unclear, despite that fact that their surgeons performing TaTME were experienced and were proctored and trained in England and Spain for the procedure.

In 1980 Knight and Griffen [19] publised their stapling technique for low rectal cancer anastomosis using linear and circular stapler. This has led to the introduction of the double stapling technique [20]. The advantage is that the distal segment of the bowel is not opened and this avoids spillage from the rectal stump.

The possibility of increased local recurrences in TaTME may be related to the rectal transection and air flow during dissection from the perineum. The rectal purse-string suture is never completely air tight and this will invariably lead to shredding of microscopic cancer cells in the pelvis and hence this may lead to an increase rate of local recurrence. During a robotic TME and the use of the articulating robotic stapler, the rectal transection is precise and there are no leakage of microscopic cancer cells in the pelvis.

With these current issues in mind, we aim to compare the 3 year disease free survival and local recurrence rate of the two procedures performed by experienced surgeons who are beyond their learning curve. Only surgeons who have performed more than 60 procedures in either TaTME or robotic TME will be selected.

ROTA study will be the first multicentre prospective trial comparing RLAR and TaTME in regards to disease free survival (DFS) and other clinical trials.

## Conclusions

There is an urgent need to assess and compare the long-term oncological outcomes of newer surgical techniques for TME (TaTME & RLAR). This will allow recommendations to be made for more tailor made treatment of rectal cancer, based on detailed outcomes from expert centers.
